## 4. Target parameters

### 4.1 Primary endpoints

The target parameters for the main hypothesis are logRSA of HRV as a marker of vagus nerve function and the inflammation markers (hs-CRP, IL-6).

### 4.2 Secondary endpoints

Blood parameters: oxidative stress markers, tryptophan metabolism, serum oxytocin, TNF-alpha, INF, IGF, neurotrophins (e.g. BDNF), salivary amylase, gut microbiome, metabolome, questionnaire scores, height, weight, BMI, gender, age, smoking habits, medication.

## 5. Methods

### 5.1 Intervention with multispecies probiotic

The multistrain probiotic and placebo used are provided by the Allergosan Institute. This is a commercially available dietary supplement called OMNi-BiOTiC® -SR, which contains 9 bacterial strains (*Bifidobacterium bifidum* W23, *Bifidobacterium lactis* W51, *Bifidobacterium lactis* W52, *Lactobacillus acidophilus* W22, *Lactobacillus casei* W56, *Lactobacillus paracasei* W20, *Lactobacillus plantarum* W62, *Lactobacillus salivarius* W24, *Lactococcus lactis* W19) with at least 7.5 trillion microorganisms per serving (=3g).

The placebo preparation will have the same colour, consistency and taste as the probiotic product. The matrix of the product contains corn starch, maltodextrin, inulin, potassium chloride, magnesium sulphate, fructooligosaccharides, amylases and manganese sulphate. Patients and healthy controls receive OMNi-Biotic SR after it has been dissolved in water and the activation time of 10 minutes has been observed. For inpatients, the study preparation is prepared daily at 7:00 a.m. by study staff and given to inpatients before breakfast and in the evening every day until discharge. After discharge, patients continue to take the preparation twice daily at home on their own. The entire study team is blinded.

## 5.2 Questionnaires

To verify the diagnosis, a M.I.N.I. is performed on depressed patients who have been admitted to the University Clinic for Psychiatry and Psychotherapeutic Medicine.

M.I.N.I. is administered. The severity of depressive symptoms is assessed using the **Hamilton Scale for Depression (HAMD)** and the **Beck Depression Inventory (BDI)**. In addition, sleep quality is assessed using the **Pittsburgh Sleep Quality Inventory (PSQI)**. Cognitive reactivity to depressive mood is assessed using the **Leids-R questionnaire**. Stress is measured using the **Trier Inventory of Chronic Stress (TICS)**. In addition, the **Perceived Stress Scale** is used to assess recent stress levels. We measure attachment behaviour using the **Adult Attachment Scale**. We also record the following clinical and demographic parameters: height, weight, BMI, gender, age, smoking habits, medication. Nutritional history is assessed using the **Vienna Nutrition Protocol** (24-hour recall), and physical activity history is assessed using the **International Physical Activity Questionnaire**. Completing these questionnaires takes approximately 1-1.5 hours.

## 5.3 Heart rate variability (HRV)

The portable ECG monitor "*eMotion* Faros" (<http://ecg.biomation.com/faros.htm>) is used to record heart rate variability. The small and portable ECG device is attached to the upper body of the participants and worn for 24 hours at the time of testing. The device is easy to use and is already being used successfully in several areas such as occupational medicine, cardiology, research, physiotherapy, sports counselling and lifestyle counselling.

[figure not shown]

**Figure 2: ECG device for recording heart rate variability. Technical details:  
ECG sampling up to 250 Hz (adjustable); HRV: 1000 Hz sampling; 3D  
acceleration (activity): sampling up to 25 Hz (adjustable).**

HRV analysis will be performed according to the Task Force guidelines (8). The following parameters are calculated to measure autonomic regulation: standard deviation of all normal-to-normal (NN) intervals (SDNN); log-transformed value of respiratory sinus arrhythmia (logRSA); the natural logarithm (ln) of high frequency (lnHF) and low frequency (lnLF) band; ln of total spectral power (lnTOT); LF/HF ratio, pulse-rate-to-respiratory-rate ratio (PRQ); and sleep duration.

#### **5.4 Microbiome analysis**

One gram of stool is collected at three test times and immediately stored in an -80°C freezer for further analysis. The microbiome is evaluated using Illumina MiSeq according to a previously published procedure (Klymiuk et al., 2017) [32]. FastQ files are used for data analysis. Quantitative Insights Into Microbial Ecology (QIIME II) is used on the MedUni Graz galaxy server to evaluate the gut microbiome (galaxy.medunigraz.at). Depending on financial resources, the metabolome (from stool) will also be analysed.

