## **Abstract**

### **Justification:**

Depression is one of the most common and serious illnesses worldwide and has a significant negative impact on patients' quality of life and ability to work. Patients with depression exhibit changes in the gut microbiome and its metabolites, which in turn influence the gut-brain axis as a bidirectional communication system. A key component of this axis is the vagus nerve, which transmits information from the internal organs in the periphery to the central nervous system. Studies have shown that the function of the vagus nerve is impaired in patients with depression. At the same time, depressed patients often have a pro-inflammatory status, which is linked to the function of the vagus nerve in influencing the immune response. Animal models have shown that vagal afferents transmit information from intestinal bacteria directly to the central nervous system and can thus induce both anxious and depressive behaviour. Stimulation of the vagus nerve (which is currently used clinically as an invasive procedure for treatment-resistant depression) has been shown to improve depression and alleviate (neuro)inflammation. A pilot study from our working group has shown that the diversity of the gut microbiome in women correlates with the function of the vagus nerve ([name]/Oberascher et al., 2020, in prep).

**Relevance:** To date, no research has been conducted into whether and to what extent probiotics can influence the function of the vagus nerve. This new mechanism could be used to specifically alter the function of the vagus nerve with probiotics and provide a rationale for add-on therapy with probiotics ("psychobiotics").

**Design:** This monocentric study will investigate the effect of a multi-strain probiotic on vagus nerve function in 40 depressed patients and 40 healthy control subjects in a placebo-controlled setting. The study participants will receive either a probiotic or a placebo for 3 months, and the function of the vagus nerve will be determined at 4 time points using a portable ECG, which will be worn for 24 hours. In addition, inflammation markers (hs-CRP, IL-6) and the gut microbiome were determined using 16S sequencing. This is the first study worldwide to investigate the effects of a multistrain probiotic on the vagus nerve in depressed patients compared to healthy control subjects. The results of this study could contribute to a better understanding of the basis of probiotic effects on mental processes.

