#### **Visit 2 Procedure:**

- Patient compliance is measured by having patients bring their daily probiotic rations back to the visit (i.e. after 1 month) and checking and noting the number of doses taken or not taken.
- Blood
- Stool (can be brought along, max. 1 day old and stored in a cool place) including stool log
- Anthropometry
- Questionnaires
- Heart rate variability (device is attached and worn for 24 hours)
- Each patient receives a ration of probiotics labelled with the respective assigned number for 2 additional months (a total of approx. 60 units).

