#### **Secondary hypotheses:**

- 1) Depressed patients show significantly higher inflammatory parameters and lower vagus function (logRSA) at the start of the study compared to healthy control subjects.
- 2) The vagus function (logRSA) and inflammatory parameters (hsCRP, IL-6) of depressed patients and healthy control subjects do not differ significantly after 3 months of intervention.
- 3) Vagus function correlates with depression scores, inflammatory parameters, oxytocin, and gut microbiota (in diversity, composition, and function) in both healthy control subjects and depressed patients.

- 4) Stool samples from the intervention group show a significantly higher proportion of short-chain fatty acids after the intervention.
- 5) The content of short-chain fatty acids in stool correlates with vagus function in healthy control subjects and in depressed patients.
- 6) Vagus nerve function correlates negatively with depression scores, sleep quality scores, subjective stress experience, and the diversity and composition of the gut microbiome.

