## 6.2 Considerations regarding the number of cases

This project is a pilot study. To the best of our knowledge, probiotic effects on vagus function in depressed patients have never been investigated before. A power analysis was performed using G\*Power 3.1.(29). In the F-tests category, the

"Repeated Measures ANOVA within-between interaction" was selected as the procedure. With a low effect size of 0.2, alpha 0.05 and 95% power, a total of 80 participants (20 participants per group) is required for 4 groups (healthy subjects: probiotic/placebo; depressed patients: probiotic/placebo).

[figure not shown]

Figure 3: Sample size calculation with G\*Power

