## 6.3 Microbiome statistics

Microbiome statistics are performed using R (v3.6) and Rstudio (1.2.1555) (R-foundation, Vienna, Austria) in collaboration with our cooperation partner [name], APC Microbiome Institute Cork. The data is visualised using the ggplot2 library. To compare the alpha diversity between the intervention and placebo groups, the Chao-1 diversity index, the Simpson index and the Shannon index are used

The diversity indices are calculated using the iNEXT library [35]. CoDa is used due to the compositional nature of microbiome data (Gloor, et al., 2017). Beta diversity is measured using principal component analysis (PCA). To correct for multiple testing, Storey's q-value post-hoc procedure is used with a q-value of 0.1 as the cut-off (30). Piphillin is used for functional microbiome analyses (prediction of metagenomic content) (31).

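### Stool handling is specified in conflicting ways across section 5.4 and the visit lists; before-after and correlation analyses of stool are exposed, the placebo comparison is not

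*Protocol*

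**What the plan says.** Section 5.4 (Microbiome analysis) gives a single rule for all samples: the stool taken at each of the three test times is "immediately stored in an -80°C freezer for further analysis".

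The visit lists in section 3 say something else. The Visit 2 list (1 month) reads "Stool (can be brought along, max. 1 day old and stored in a cool place) including stool log", and the follow-up appointment (3 months) carries the same line. The Visit 1 list names stool as an item and adds nothing on age, storage or a log.

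Three other places bear on the consequences:
- The trial is randomised and placebo-controlled, and section 5.1 states "The entire study team is blinded".
- Section 6.3 sets the alpha-diversity contrast as one between arms: "To compare the alpha diversity between the intervention and placebo groups".
- Secondary hypothesis 4 in section 3.2 names no comparator: "Stool samples from the intervention group show a significantly higher proportion of short-chain fatty acids after the intervention". Hypotheses 3, 5 and 6 correlate vagus function with gut microbiota or stool short-chain fatty acids.

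**The concern.** A sample that may wait up to a day outside a freezer has not been frozen immediately, so the two rules do not agree as written. The conditions also differ by visit: the allowance and the log belong to the two follow-up visits only.

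Patients are recruited as inpatients (section 2), and after discharge they continue the preparation at home (section 5.1). Healthy controls are recruited from the public (section 3). Time from stool to freezer could therefore differ between a patient's baseline and later samples, and between patients and controls. If handling alters the measured microbiome or short-chain fatty acids, a change over time or a correlation could partly reflect storage. With no log listed at Visit 1, baseline delay could be neither described nor adjusted for later.

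**Working it through.** **1. The rules side by side**

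| Place in protocol | Time point | Maximum age | Storage before -80 °C | Stool log |
|---|---|---|---|---|
| Section 5.4 | all three | none (immediate freezing) | none | not mentioned |
| Visit 1 list | baseline | not stated | not stated | not listed |
| Visit 2 list | 1 month | 1 day | cool place | yes |
| Follow-up appointment list | 3 months | 1 day | cool place | yes |

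The first row agrees with the last two only if immediate freezing means freezing on receipt at the clinic. The text does not say so.

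**2. How many samples the allowance covers**

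Section 6.2 plans 80 participants. Three samples each gives 80 × 3 = 240. The two follow-up visits give 80 × 2 = 160. So up to 160 of 240 samples may be a day old. This is a ceiling on what is permitted and does not estimate how many will be late.

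**3. Which contrasts a handling shift can bias**

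Let a delayed sample be shifted by h standard deviations (SD). Let p0 be the delayed share at baseline and p1 the share at follow-up, the same in both arms, with no treatment effect.
- Expected change within an arm: (p1 − p0) × h.
- Expected difference in change between arms: (p1 − p0) × h − (p1 − p0) × h = 0.

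The protocol has no figure to reproduce here, so this was illustrated by simulation with 10,000 runs per setting. Group sizes come from section 6.2 ("a total of 80 participants (20 participants per group) is required for 4 groups"): n = 20 per group, or 20 × 2 = 40 per treatment arm. The shift h, the delayed shares and a baseline-to-follow-up correlation of 0.5 are assumptions. Tests are two-sided at 0.05: a one-sample t-test of change within the probiotic arm, and a two-sample t-test of change between arms.

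False-positive rate of the within-arm test:

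| Delayed share (baseline → follow-up) | n | h = 0.3 | h = 0.5 | h = 0.8 |
|---|---|---|---|---|
| none → all | 20 | 26% | 57% | 93% |
| none → all | 40 | 46% | 87% | 99.8% |
| none → half | 20 | 10% | 18% | 35% |
| none → half | 40 | 15% | 33% | 63% |

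In these same 12 settings the between-arm test stays at 4.7% to 5.4%, with a mean difference of about 0.00. When half the samples are delayed at both time points, both tests are near 5% (within 4.6% to 5.3%, between 4.4% to 5.3%).

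The size is plausible by hand. With correlation 0.5 the variance of change is 2 × (1 − 0.5) = 1, so for h = 0.5 and all follow-up samples delayed the expected t ratio is about 0.5 × √20 = 2.24 for n = 20 and 0.5 × √40 = 3.16 for n = 40.

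**4. Correlations**

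Hypotheses 3, 5 and 6 are not randomised comparisons. If delay is related both to the stool measure and to vagus function, it can induce a correlation between them. Section 1 reports lower heart rate variability in depressed patients, so a delay that tracks diagnosis would provide such a link wherever patients and controls are pooled. Hypotheses 3 and 5 can be read as separate analyses within each group, which removes that link but not one through discharge status among patients. Hypothesis 6 names no group.

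**The case against.** A reader might infer that handling is mixed with the treatment effect itself. The documents do not support that. Both arms follow the same rule, the study team is blinded, and a common shift cancels. It would survive only if delay were more frequent in one arm, or if delay acted differently on stool containing live probiotic strains. The protocol gives no evidence for either.

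A reader might also infer that every patient has a fresh baseline sample and a day-old follow-up sample. That is conjecture. The Visit 1 list is silent on sample age, and the later lists permit a brought-along sample without requiring one. A patient still on the ward at Visit 2 could give a fresh one.

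It is also fair to say that immediate freezing may mean on receipt, that a maximum age, cool storage and a log already exist for two visits, and that the log may already record times, since its contents are not shown. Hypothesis 4 can be read against placebo. Section 5.4 makes the stool metabolome conditional on funding. No listed hypothesis compares stool between patients and controls, and the primary endpoints (logRSA, hs-CRP, IL-6) use no stool.

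All of this limits the reach of the point. It does not remove the conflict in wording, the gap at Visit 1 or the exposure of the non-randomised analyses. Nor can it be left to an analysis plan, because a time that was never recorded cannot be recovered.

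**Conclusion.** The contradiction between section 5.4 and the visit lists is real, and the passages must be reconciled. Its consequence is limited to secondary analyses: change within an arm, which matters for hypothesis 4 on a before-after reading, and the stool correlations in hypotheses 3, 5 and 6. The randomised comparison of probiotic with placebo is protected against a handling shift common to both arms.

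The true size of any handling effect is unknown. The simulated range, from 10% to 99.8% false positives for a within-arm test, rests entirely on the assumed shift (0.3 to 0.8 SD), delayed share (half or all at follow-up, none at baseline) and correlation (0.5). It shows which analyses are vulnerable and does not predict how far this trial will be affected. The point is worth acting on because the remedy is cheap and must be in place when samples are taken.

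**What to change.** - Write one handling rule, with the same maximum age and the same storage condition, for all three time points and both diagnosis groups. State it identically in section 5.4 and in the Visit 1, Visit 2 and 3-month lists.
- If samples from home are accepted, replace the requirement for immediate freezing in section 5.4 with freezing on receipt.
- Use the stool log at Visit 1 too, and have it record the time the stool was passed and the time it was frozen.
- State hypothesis 4 as a comparison of probiotic with placebo.
- Use time to freezing only as an adjustment in a sensitivity analysis. Do not drop late samples from the main analysis: that would be an exclusion after randomisation, with only 20 participants per group.

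The cost is protocol wording and slightly more logging at Visit 1. One constraint needs planning: the first dose is taken at Visit 1, so the baseline sample must meet the rule before that dose. It cannot be re-collected afterwards as a pre-treatment sample.

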#### **5.5 Blood sampling**

Blood samples are taken from all participants in the morning on an empty stomach. A maximum of 70 ml of blood is taken in total. After blood collection, the plasma is centrifuged at 4000 rpm for 15 minutes and stored at -20 °C for further analysis. C-reactive protein (CRP) and (IL)-6 are analysed at the Institute for Laboratory Diagnostics ([name], Doz. [name]) using Cobas 6000 (Roche Diagnostics, Mannheim, Germany).

The following parameters are also determined:

Routine parameters: blood count including differential blood count, liver values, kidney values, lipids, CRP, IL-6, glucose metabolism

Biomarkers: oxidative stress parameters, oxytocin, neuroinflammatory markers (e.g. interleukins, TNF  $\alpha$ , INF, tryptophan metabolism, IGF), neurotrophins (e.g. BDNF), depending on the available budget from funding, the samples are analysed immediately or stored in the meantime.

## 5.6 Saliva sample

At the time of inclusion in the study and after 1 and 4 weeks, alpha-amylase in saliva will be measured as a stress marker, provided sufficient funding can be secured. Salivary amylase is elevated as a stress marker in depressed patients (26). Studies have shown that probiotics can influence alpha-amylase in athletes or surgical patients (27, 28) – whether probiotics can influence salivary amylase in depressed patients has not yet been investigated. A saliva sample is required to determine alpha-amylase. It is obtained non-invasively by the participants themselves using a Salivette (Sarstedt, Germany) in accordance with the test instructions (on an empty stomach, without brushing their teeth or using mouthwash beforehand), then centrifuged and frozen until analysis. The evaluation will be carried out in collaboration with the Otto Loewi Research Centre for Pathophysiology and Immunology.

## 6. Statistics

### 6.1 Randomisation

The study design results in 4 groups:

- **Depressed patients Probiotics/placebo**
- **Healthy subjects: probiotics/placebo**

The subjects are using computer-assisted **4-person block randomisation** (randomisation.com).

## 6.1 Data analysis and evaluation

The data obtained will be analysed using IBM SPSS, version 27. A descriptive data description (mean, standard deviation, percentile rank) will be provided. Correlations between variables will be calculated using Pearson's correlation coefficient or Spearman's correlation coefficient, depending on the distribution. Error probabilities below  $p < 0.5$  are considered statistically significant. Microbiome analyses are performed in R (version 3.6) and Rstudio (version 1.2.1555) (R-doundation, Vienna, Austria), with visualisations using the ggplot2 library.

Both an intention-to-treat and a per-protocol analysis are performed.

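### Secondary hypotheses 3, 5 and 6 rest on unadjusted correlations, while age, sex, BMI, smoking and medication are collected but listed as endpoints instead of covariates

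*Protocol*

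**What the plan says.** Protocol section 6.1 (Data analysis and evaluation) gives one method for associations: "Correlations between variables will be calculated using" either the Pearson or the Spearman coefficient, whichever suits the distribution. Neither that section nor section 6.3 (Microbiome statistics) names a partial correlation, a regression or a covariate.

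Three of the six secondary hypotheses in section 3.2 are association hypotheses:

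- Hypothesis 3, in both populations: "Vagus function correlates with depression scores, inflammatory parameters, oxytocin, and gut microbiota".
- Hypothesis 5: "The content of short-chain fatty acids in stool correlates with vagus function in healthy control subjects and in depressed patients".
- Hypothesis 6, with no population named: "Vagus nerve function correlates negatively with depression scores, sleep quality scores, subjective stress experience", and also with microbiome diversity and composition.

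Section 5.2 records body size, gender, age, smoking and medication as clinical and demographic parameters. Section 4.2 places the same items among the secondary endpoints: "questionnaire scores, height, weight, BMI, gender, age, smoking habits, medication". Section 3.1 admits ages 18 to 65 and sets no limit on sex, BMI, smoking or ordinary medication.

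**The concern.** Age, for example, can plausibly influence both logRSA and an inflammatory marker. If it does, the two will correlate within a group of mixed age even when neither acts on the other. A bivariate coefficient cannot distinguish this from a direct link. The protocol collects the variables needed to examine the question but gives them no such use. Age and gender cannot be outcomes of a probiotic, so listing them as endpoints is a misclassification and not merely a gap.

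What is at stake is the interpretation of hypotheses 3, 5 and 6. Section 1 already moves from a pilot correlation between diversity and vagus function to an interaction between microbiome, inflammation and vagus nerve. A crude coefficient from this trial could be read in the same way.

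**Working it through.** **The plan's own figure.** Section 6.2 gives N = 80 for a repeated-measures ANOVA interaction with effect size f = 0.2, alpha 0.05, 95% power and 4 groups. The Abstract gives 4 time points. The text does not state the correlation between repeated measures or the sphericity correction; assume 0.5 and 1.

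- Noncentrality: 0.2² × 80 × 4 / (1 − 0.5) = 25.6
- Degrees of freedom: 3 × 3 = 9 and (80 − 4) × 3 = 228
- Power: 0.960, and N = 80 is reproduced

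This calculation concerns the ANOVA interaction. It says nothing about the correlations.

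**Inputs for the correlations.**

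- n = 40 per population (Abstract).
- Two-sided alpha 0.05, taken from section 6.2. Section 6.1 prints the threshold as 0.5, a separate discrepancy that needs its own correction.
- The documents give no correlation of age, BMI or smoking with logRSA or any marker. The values a and b below are therefore assumptions.

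**Formula.** Let one factor C correlate a with vagus function and b with the marker, with no direct link between the two. The crude correlation is then r = a × b. By Fisher's approximation the test statistic is centred at m = atanh(|r|) × √(n − 3), and the rejection rate is Φ(−1.96 + m) + Φ(−1.96 − m). With n = 40, √37 = 6.083.

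- a = −0.3, b = 0.3: r = −0.09, m = 0.549, rate 0.079 + 0.006 = 8.5%
- a = −0.5, b = 0.3: r = −0.15, m = 0.919, rate 0.149 + 0.002 = 15.1%
- a = −0.4, b = 0.4: r = −0.16, m = 0.982, rate 0.164 + 0.002 = 16.6%
- a = −0.5, b = 0.5: r = −0.25, m = 1.554, rate 0.342 + 0.000 = 34.2%

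**Simulation of the same settings** (40,000 samples each). The crude test rejects in 8.5%, 15.3%, 16.4% and 34.9%. The partial correlation given C rejects in 4.8% to 5.1%. At a = −0.6, b = 0.6 the crude rate is 64.4%, which shows how strongly the result depends on the assumption.

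**Two factors together.** If independent age and BMI factors correlate −0.5 and −0.2 with logRSA, and 0.3 and 0.5 with log CRP, then r = (−0.5 × 0.3) + (−0.2 × 0.5) = −0.25. A simulation of 5,000 samples gave 33.9% for the crude test.

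**Pooling.** Hypothesis 6 names no population. If all 80 participants were pooled, the crude rate for a = −0.3, b = 0.3 would be 12.7%, and for a = −0.5, b = 0.5 it would be 61.3%.

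**Cost of adjustment at n = 40.** The standard error of Fisher's z is 1/√(37 − q) with q covariates. It is 0.164 unadjusted, 0.171 with three covariates (4% larger) and 0.174 with four (6% larger).

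**Limit.** The percentages apply to single tests at 0.05. They do not carry over to microbiome features, for which section 6.3 sets a q-value cut-off of 0.1.

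**The case against.** The strongest reply is that these are secondary hypotheses in a self-described pilot, that they say only that variables correlate, and that a simple coefficient answers that wording. This stands, and it limits the weight of the point. The main evidence on the probiotic is the randomised comparison of logRSA, IL-6 and hs-CRP, which confounding of the correlations does not touch.

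A second reply is that the statistical analysis plan, not shown here, may add adjusted models. It may. But the protocol names the method, so the point concerns stated text and not only silence.

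A third is that section 3.1 already excludes known cardiovascular disease, acute infection, tumours and severe autoimmune disease. That removes some shared causes, but age, sex, BMI and smoking remain open.

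A fourth is that BMI may lie on the pathway between microbiota, inflammation and vagal function, so adjusting for it could remove a real association. Medication is awkward too: its coding is not defined, and a yes/no variable may hardly vary among treated inpatients. Both objections stand and shape the fix.

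Some stronger readings are tempting and are not supported:

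- *That confounded links will be reported as mechanism.* No section says so. The passage in section 1 shows the risk, not a plan.
- *That the bias favours the expected result.* Hypotheses 3 and 5 state no direction.
- *That the false-positive rate is far above 5%.* With correlations of about 0.3 it is 8.5%.
- *That the pilot finding applies to women only.* The Abstract says "the diversity of the gut microbiome in women correlates with the function of the vagus nerve", but section 1 reports the correlation without that restriction, and the manuscript is not available.

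**Conclusion.** The point holds in a limited form. The protocol names only unadjusted coefficients for hypotheses 3, 5 and 6, and it gives the recorded participant characteristics a role as endpoints but none as covariates. A shared cause may therefore appear as an association of vagus function with inflammation or the microbiome.

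How large the effect is cannot be known from the documents. The range of about 8% to 35% false positives rests on a single shared factor correlating 0.3 to 0.5 with both variables, no direct link, n = 40 and alpha 0.05. The case for a change is that the remedy costs little and needs no new data. It is not that a false result has been shown to be likely. Neither the randomised comparison nor N = 80 is affected.

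**What to change.** In section 6.1, state that hypotheses 3, 5 and 6 will be examined within each population by a partial (rank) correlation or a linear regression adjusted for age, sex and smoking, with a 95% confidence interval. When post-baseline data are used, add the randomised arm, because each population of 40 combines 20 probiotic and 20 placebo participants. Report the crude Pearson or Spearman coefficient beside it, labelled descriptive.

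Add one sensitivity analysis that also adjusts for BMI and, in patients, for medication with its coding defined in advance. State that BMI may be a mediator. In section 4.2, move height, weight, BMI, gender, age, smoking and medication from the endpoint list to a list of covariates.

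The cost is wording and a standard analysis option. If smoking is a single variable, the main model uses three degrees of freedom per population, or four with arm (38 falls to 35 or 34), and the standard error rises by about 4% to 6%.

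### The general significance threshold is written as p < 0.5, a 50% false-positive rate per test, against the alpha of 0.05 used to size the trial

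*Protocol*

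**What the plan says.** Section 6.1 (Data analysis and evaluation) gives the software, the descriptive statistics and the choice between Pearson and Spearman correlation, and then the decision rule: "Error probabilities below $p < 0.5$ are considered statistically significant". No other general p-value threshold appears in the protocol.

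Section 6.2 (number of cases) works at a different level: "With a low effect size of 0.2, alpha 0.05 and 95% power, a total of 80 participants (20 participants per group) is required". The calculation is a G*Power F-test for the within-between interaction of a repeated-measures ANOVA.

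Section 6.3 sets one separate rule, for multiple testing in the microbiome statistics: "Storey's q-value post-hoc procedure is used with a q-value of 0.1 as the cut-off".

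In section 3.2, the primary hypothesis and secondary hypotheses 1, 2 and 4 are phrased as the presence or absence of a significant difference or change. Secondary hypotheses 3, 5 and 6 are correlations.

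**The concern.** The two thresholds differ tenfold, and the wrong one sits in the rule that governs the analyses. Read literally, section 6.1 lets any result with p just under 0.5 count as significant, so a treatment with no effect would be declared effective on a given marker half the time. Because the hypotheses are decided by whether a result is significant, this figure fixes the trial's conclusions directly. A threshold is prespecified so that nobody has to choose it after seeing the data. A reader of section 6.1 alone has no usable threshold, and a reader of both sections has two.

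**Working it through.** **1. Which alpha the design rests on**

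Inputs from section 6.2: effect size 0.2 (taken as Cohen's f, as G*Power uses for F-tests), alpha 0.05, power 95%, k = 4 groups, N = 80.

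Inputs not stated there: m = 4 repeated measurements, from the abstract ("the function of the vagus nerve will be determined at 4 time points using a portable ECG"); correlation between repeated measures ρ = 0.5 and nonsphericity ε = 1, both assumed because the G*Power figure is not available.

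Formulas for the within-between interaction, with ε = 1:

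- λ = f² × N × m / (1 − ρ)
- df1 = (k − 1)(m − 1)
- df2 = (N − k)(m − 1)

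At N = 80:

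- λ = 0.04 × 80 × 4 / 0.5 = 25.6
- df1 = 3 × 3 = 9
- df2 = 76 × 3 = 228

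| Threshold | Smallest N for 95% power (multiples of 4) | Power at N = 80 |
|---|---|---|
| 0.05 | 80 (N = 76 gives 0.948) | 0.9595 |
| 0.5 | 36 | 0.9993 |

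The planned 80 is reproduced exactly at 0.05 and not at 0.5. Sensitivity with four groups, over m = 2 to 4 and ρ = 0.3 to 0.7: required N runs from 48 to 156 at 0.05, which includes 80, and from 24 to 64 at 0.5, which never reaches it.

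**2. Error rate if section 6.1 is applied as written**

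Per test, the type I error equals the threshold: 50% instead of 5%.

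The three primary markers in section 4.1 are logRSA, hs-CRP and IL-6. The protocol does not say whether success needs one marker or all three, so both readings are shown, with no true effect on any marker. The independent case is exact: 1 − (1 − α)³ for at least one, α³ for all three. The correlated case is a simulation of three equicorrelated normal statistics, two-sided, at r = 0.5.

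| Reading | Threshold 0.5: independent | Threshold 0.5: r = 0.5 | Threshold 0.05: independent | Threshold 0.05: r = 0.5 |
|---|---|---|---|---|
| At least one marker | 1 − 0.5³ = 87.5% | 84% | 1 − 0.95³ = 14.3% | 12.5% |
| All three markers | 0.5³ = 12.5% | 17% | 0.05³ ≈ 0.01% | 0.3% |

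**3. Correlations**

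The threshold sentence directly follows the one on correlation methods. The smallest |r| that counts as significant is t / √(n − 2 + t²), where t is the two-sided critical value on n − 2 degrees of freedom.

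| n | Threshold 0.05 | Threshold 0.5 |
|---|---|---|
| 40 (patients or controls) | 0.312 | 0.110 |
| 80 (all participants) | 0.220 | 0.077 |

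At 0.5, a correlation explaining about 1% of the variance (0.110² ≈ 0.012) would be reported as significant in 40 people.

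**The case against.** The strongest reply is that this is a dropped zero which nobody would apply. Section 6.2 states 0.05, the sample size fits 0.05, and the same paragraph of section 6.1 contains another typing slip. An analyst would very probably use 0.05, so the practical risk is well below what the literal reading suggests. That is fair, and it determines how the point should be read: as a correction, not as evidence that the sponsor intends a 50% error rate. It does not remove the point, because the figure stands in the protocol's only general decision rule. A statistical analysis plan using 0.05 would contradict the protocol until the protocol is amended.

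A fault in reading the PDF cannot be wholly excluded. Nothing suggests one, though: a p < 0.01 in section 1 and the 0.05 in section 6.2 both came through intact. A look at the original page settles it.

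Two limits on scope stand. The rule does not cover microbiome tests handled under the q-value cut-off of 0.1. The 87.5% and 84% also assume that one significant marker out of three would be claimed as success. H1 joins the markers with the word and; if all three are required, the figures are 12.5% and about 17%. Those are still far above the 0.01% and 0.3% at a threshold of 0.05, so neither reading rescues 0.5.

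**Conclusion.** The concern holds. Section 6.1 states a threshold ten times the alpha in section 6.2, and no other part of the protocol resolves the difference. The contradiction and the 50% against 5% error per test rest on no assumption. The three-marker figures depend on how success is defined and on the correlation between markers. The exact match to N = 80 depends on four time points, ρ = 0.5 and ε = 1; it serves only to show that 0.05 is almost certainly the intended value. This must be corrected, because any claim of significance made under the rule as written could not be interpreted.

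**What to change.** In section 6.1, change the threshold to p < 0.05, matching section 6.2, and state that the q-value cut-off of 0.1 in section 6.3 applies only to the microbiome statistics. It is sensible to say in the same sentence that tests are two-sided. The protocol does not state sidedness and the sample-size F-test does not settle it, so that is a clarification separate from the correction itself.

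The cost is one corrected figure in a protocol amendment. Under the assumptions above, the sample size stays at 80 with power 0.96. The correction does not deal with multiplicity across the three primary markers: the chance of at least one false positive at 0.05 remains 14.3% if they are independent, which is a separate question.
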